***Description of FAM-CARE Service Program***

EGPAF-Swaziland is piloting a FAM-CARE program, implemented with program funding prior to initiation of the current study. Viral load monitoring is in the process of being implemented at all HIV care sites in Swaziland. For implementation of the FAM-CARE program, EGPAF-Swaziland has randomly selected one hospital and one health center and its cluster clinics (Emkhuzweni cluster and Pigg’s Peak cluster) as FAM-CARE sites and one hospital and one health center and its filter clinics (Dvokolwako cluster and Mbabane cluster) which continue their current standard of HIV care (separate pediatric and adult HIV clinics) and serve as control comparison sites. A brief description of the FAM-CARE program that has been implemented at the selected sites is provided below.

*Enrollment of patients into the FAM-CARE program*

Children receiving HIV care and treatment services at the selected FAM-CARE facilities will be the primary starting point for identifying other HIV-positive family members to be enrolled into care. The children will be recruited primarily from the HIV care and treatment departments, and in any other units within the health facility such as maternal/child health programs or PMTCT follow-up programs. After identifying a child receiving HIV treatment services, the health care worker will talk to the mother or caregiver about the FAM-CARE program within the health facility.

The adult who has brought the child to the facility will be asked the following questions:

1. If they are also HIV-positive and receiving care and treatment services. If yes, they would be invited to participate in the FAM-CARE initiative at the facility.
2. If any of their family members (spouse, children etc.) are also HIV-positive and receiving care and treatments services. If yes, an invitation letter will be issued inviting all family members to come to the health facility to participate in the FAM-CARE program at the facility if feasible. If needed, the facility health care workers will facilitate transfer out from other facilities for family members receiving HIV care at another facility. Even if the family members are not on ART but are known to be HIV-positive, they will be invited to participate in the FAM-CARE program.

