*Before a scheduled family visit* to the facility, designated health care workers and expert clients (a trained, HIV-positive lay person responsible for educating, counseling, and supporting other HIV-positive clients to understand, manage, and cope with their chronic illness at the health facility level) will pull out the family folder and prepare the ART medication for the family in advance.

*Upon arrival* at the facility, the family will be directed to a designated expert client who will take them to a consultation room where they will receive the required services. Separate consultation for individual family members may be conducted if needed for sensitive topics. In clinics the family will be prioritized over individual clients in order to decrease waiting time, whilst in hospitals or health centers the families will be seen on special days that will be set aside as family-days. If none of the family members is unwell, pre-packed medication will be dispensed by the expert client. However, if a member is unwell, the health care worker will be availed to consult and manage the member. After enrollment into the FAM-CARE program, if the family members are all stable (e.g., virally suppressed on ART), only one family member can visit the health facility to collect the medication for the entire family (except for children who might need dose adjustment based on weight). Other family members will be seen at the health facility only during the stipulated dates for monitoring and as when required. Viral load testing will be conducted on all family members at the same visit (every six months).

*After leaving the facility*, family units will be reminded of their upcoming appointments through text messages three days before the appointment date. If a family unit does not return for their appointment, they will be followed up using routine client follow up processes in the supported facilities.

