The Hhohho region consists of 4 clinic “clusters”; there was random selection (“coin toss” selection) of “clusters” to initiate FAM-CARE vs to continue standard of care. The FAM-CARE program is being initiated at two “clusters” of clinics that were randomly selected while the other two “clusters” will continue standard of care. The Emkhuzweni and Pigg’s Peak clusters were randomly selected to initiate FAM-CARE, while the Dvokolwako and Mbabane clusters will continue standard of care. For the **prospective** **study evaluation of the FAM-CARE program,** enrollment will take place at selected FAM-CARE and control sites, consisting of the hospital/ health center “parent” of the cluster plus the largest filter clinic for the cluster. Thus, study facilities will include 4 facilities that were randomly assigned to initiate the FAM-CARE program (one hospital plus one filter clinic and one health center and one filter clinic) (FAM-CARE site enrollment) and 4 facilities that were randomly assigned to remain standard of care (one hospital plus one filter clinic and one health center and one filter clinic) (control site enrollment) (see **Table 2** below for facilities/patient numbers). However, we may also expand to include additional filter clinics if necessary.

**Table 2:** Cluster Facilities & Number of Children on ART in Study Facilities

| **Facilities (that have been randomized to FAM-CARE program vs control sites) that will enroll children in the FAM-CARE program evaluation** | | **Children 0-14 Years on ART 31 December 2015** | |
| --- | --- | --- | --- |
| **Facility Name** | **Facility Type** | **Initiated on ART** | **Currently on ART** |
| **Dvokolwako Cluster (Control)** | | | |
| Dvokolwako Health Centre | Health Centre | 32 | 203 |
| Balekane Nazarene Clinic | Clinic | 9 | 36 |
| *Total* |  | *41* | *239* |
| **Mbabane Cluster (Control)** | | | |
| Mbabane Govt | Hospital | 22 | 248 |
| Lobamba ART Clinic | Clinic | 25 | 88 |
| *Total* |  | *47* | *336* |
| **Emkhuzweni Cluster (Intervention)** | | | |
| Mkhuzweni HC | Health Centre | 28 | 159 |
| Mangweni | Clinic | 17 | 64 |
| *Total* |  | *45* | *223* |
| **Pigg's Peak Cluster (Intervention)** | | | |
| Pigg’s Peak Hospital | Hospital | 22 | 318 |
| Horo | Clinic | 3 | 80 |
| *Total* |  | *25* | *398* |

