We will enroll all HIV-positive children with >1 family member who is also HIV-positive seen at the study facilities until we have achieved the desired sample size total of 444 HIV-positive children from unique families receiving ART at enrollment (see *Statistical Methods*). We estimate we will need to enroll approximately 666 HIV-positive children into the study (333 per arm) to achieve the target sample size of 444 HIV-positive children receiving ART from unique families (222 per arm).

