***Recruitment***

Eligible HIV-positive children age <15 years and their caregivers from families with at least one additional HIV-positive family member residing in the household at study sites will be identified and referred by clinic staff to the site study nurse, who will explain the study and study procedures. The study nurse will conduct the informed consent procedures with eligible caregivers and informed assent discussion with older children (> 12 years to <15 years) in a private location with a witness present in the case of an illiterate participant. The informed consent form (and informed assent form when relevant) will be read to the caregiver/child and h/she will be given the opportunity to ask questions. Written informed consent will be obtained from the mother/caregiver prior to any study procedures being conducted. Mothers under the age of 18 years will be treated as mature (emancipated) minors and able to provide informed consent for themselves and their children. After obtaining written informed consent from the caregiver, the study nurse will seek verbal informed assent from children >12 to <15 years of age. Once informed consent (and informed assent as appropriate) are obtained, participants will be enrolled in the study and assigned a participant study identification number that will include a family identification designation for all enrolled family members. Enrollment will continue in each site until the targeted number of HIV-positive children have been enrolled.

Informed consent will be sought from other HIV-positive adult (>18 years) family members at both FAM-CARE and control sites for abstraction of HIV-related clinical and laboratory data from medical records. For HIV-positive adolescents between the ages of 15 through 17 years, informed consent for data abstraction from existing medical records will be obtained from the mother/caregiver. However, this will not be required to enroll a child into the study. HIV-positive adults in the family who provide informed consent will be assigned a participant study identification number that includes a family study identification designation.

*Statistical Methodology*

*Sample size estimation*

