**ii. Research Protocol/Methods**

1. ***Study Procedures***

After obtaining written informed consent from the caregiver and verbal informed assent from children < 12 years, eligible HIV-positive children will be enrolled in the study into the FAM-CARE or control arm depending on the facility h/she attends. An enrollment visit will be conducted, during which caregivers will be interviewed to collect demographic, medical and HIV-related information about the child. Clinical/laboratory data will be abstracted from clinic medical records. The caregiver will be interviewed regarding HIV infection status of other family members and clinical/treatment history obtained for other HIV-positive family members by interview and chart abstraction. Children will be seen for a study-specific visit at enrollment and every three months by study staff. Study visits will be scheduled to coincide with routine health services visits to the child as much as possible.

At each study visit, the study nurse will obtain interim clinical history (e.g., medical/HIV history and CD4 count and, for children on treatment, ART history, current regimen, and adherence questionnaire) by caregiver interview and abstraction of clinical and laboratory data from medical records and record on study data collection tools. Clinic visit attendance and pharmacy drug pick-up for children receiving ART will be obtained by chart abstraction. Blood will be drawn from the HIV-positive children on ART for study viral load testing at enrollment and at 6, 12, and 18 months on study. HIV-positive children not on ART at enrollment who initiate ART during study follow-up will have viral load testing at ART initiation and every six months during the study. Table 3 shows the proposed schedule of data collection.

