***c) Data Collection and Management***

1. *Data collection procedures*

Study-specific visits will be conducted at the study site by the study nurse, and be timed to coincide with routine health care visits whenever possible. Medical record abstraction will be performed by the study site nurse. Study nurses will be present in each study facility and will be responsible for the collection, maintenance of study records and data, and collection of viral load specimens. Informed consent documents, study screening/enrollment logs, and participant locator forms that include identifiable information will be completed at enrollment and stored in a locked secure location in the health facility with access limited to study staff. After all data collection is completed, the study records will be stored in central storage in EGPAF-Swaziland offices under the same strict controls.

Data will be collected and entered into electronic tablets by direct data entry into a database that will be designed specifically for this study and stored on a secure web-based server. Built-in data checks will ensure that data are within a feasible range. Any out of range values will be verified by looking through the source document. In facilities that do not have wi-fi access for immediate uploading of data, data will be stored temporarily on the tablet, and subsequently transferred to the web-based server on a routine basis. There will be controlled access to the web-based database by study staff with specific IDs and permissions depending on their study role, both for the study team in EGPAF/Swaziland and EGPAF/United States.

1. *Data collection instruments*

The study data collection instruments will be designed in English and pilot tested by the study team prior to use. Some data components in the participant interview may require translation into SiSwati to ensure accurate and consistent interpretation. The management and conduct of study visits will be the responsibility of the site study nurse. The study nurse will work closely with the study coordinator, who will be responsible for oversight of the data collection by study nurses, to ensure quality of the data collected.

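### Clinic staff who know the arm refer children until a quota is met, and neither the register nor an enrolled-versus-not-enrolled check guards against differential selection

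*Protocol*

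**What the plan says.** **Arm known in advance.** The FAM-CARE programme was "implemented with program funding prior to initiation of the current study" (Description of FAM-CARE Service Program). The Emkhuzweni and Pigg's Peak "clusters were randomly selected to initiate FAM-CARE, while the Dvokolwako and Mbabane clusters will continue standard of care" (Data Gathering Activity 1, Subject Population). Children "will be enrolled in the study into the FAM-CARE or control arm depending on the facility h/she attends" (Study Procedures).

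**Route of entry.** Eligible children and caregivers "will be identified and referred by clinic staff to the site study nurse, who will explain the study and study procedures" (Recruitment).

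**Stopping rule.** The study takes all eligible children "seen at the study facilities until we have achieved the desired sample size total of 444 HIV-positive children from unique families" (Subject Population, text after Figure 1). Recruitment adds: "Enrollment will continue in each site until the targeted number of HIV-positive children have been enrolled". Study sampling procedures repeats the intention to enrol all children under 15 until the target is met. It gives no list, order or sampling rule.

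**Attendance.** Monthly visits are described as usual for children, both in the regional service description and within the FAM-CARE description. In FAM-CARE families whose members are all stable, "only one family member can visit the health facility to collect the medication for the entire family". The same sentence excepts children who may need a weight-based dose change.

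**Safeguards.** Data collection procedures mentions screening and enrolment logs and says that "Study nurses will be present in each study facility". The Statistical Analysis Plan section compares baseline characteristics by arm, adjusts for imbalances and adds an intent-to-treat comparison by facility. Its one named check for selection bias compares families who decline FAM-CARE with those who accept it, inside FAM-CARE sites.

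**The concern.** Randomising clusters makes the facilities' populations comparable in expectation. It does not protect the comparison when individuals are recruited after allocation by people who know the arm. What is compared at 18 months is the enrolled children, and enrolment depends on being seen, being referred and arriving before the quota closes. At FAM-CARE sites, facility health workers also deliver the programme being evaluated. If referral or attendance depends on how well a child is doing, and does so differently by arm, the enrolled suppression rates differ for reasons unrelated to the programme. This could create an apparent effect or hide a real one.

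The listed safeguards do not close this gap. Adjustment covers measured characteristics of enrolled children. The decliner check concerns uptake of the programme, not entry to the study. The intent-to-treat comparison deals with programme refusal; because the Confidentiality section says individual data on non-participants will not be collected, it can include only enrolled children.

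**Working it through.** **1. The plan's own figure.** Table 3 inputs: 80% vs 90% suppression, alpha 0.05 (taken as two-sided), power 80%.

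n per arm = [1.96 × √(2 × 0.85 × 0.15) + 0.8416 × √(0.8 × 0.2 + 0.9 × 0.1)]² / 0.10² = [0.990 + 0.421]² / 0.01 ≈ 199.

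With 10% loss, 199 / 0.9 = 221.1, rounded up to 222 per arm, or 444 in total. The plan's figures reproduce.

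**2. The pool.** Children on ART at the study facilities (Table 2, 31 December 2015):
- Intervention: 223 + 398 = 621
- Control: 239 + 336 = 575

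**3. The number enrolled.** The plan enrols 333 children per arm and assumes 15% are not on ART: 333 × 0.85 = 283 on ART per arm.

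**4. Share of the pool enrolled.** The protocol expects that no more than 10-20% of HIV-positive children will fall outside FAM-CARE, for lack of an HIV-positive relative or because of disclosure. Using that range as the ineligible share for the study is an assumption.

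| Denominator | Intervention | Control |
|---|---|---|
| All on ART | 283/621 = 46% | 283/575 = 49% |
| Eligible if 10% ineligible | 283/559 = 51% | 283/518 = 55% |
| Eligible if 20% ineligible | 283/497 = 57% | 283/460 = 62% |

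So roughly 38-49% of eligible children on ART would not be enrolled. If 90% rather than 85% of enrolled children are on ART (the upper end of the protocol's range), 333 × 0.90 = 300, which is 48% and 52% of all on ART.

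**5. What selection could do (illustration on assumed inputs).** Let true suppression be 80% in both arms and let one arm's cohort be representative. In the other arm, suppressed children are R times as likely to be enrolled as unsuppressed children:

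enrolled rate = 0.8R / (0.8R + 0.2)

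| R | Enrolled rate | Shift |
|---|---|---|
| 1.25 | 1.0/1.2 = 83.3% | +3.3 points |
| 1.5 | 1.2/1.4 = 85.7% | +5.7 points |
| 2 | 1.6/1.8 = 88.9% | +8.9 points |
| 0.8 (opposite direction) | 0.64/0.84 = 76.2% | −3.8 points |

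The design effect is 10 points. No value of R comes from the documents.

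**6. Direction.** The only attendance difference documented is that stable FAM-CARE families may send one member. To the extent that children are covered by it, suppressed FAM-CARE children are seen less often and R falls below 1, which dilutes the effect. Preferential referral of well-controlled children would push R above 1, but nothing in the protocol describes it.

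**The case against.** **Consecutive entry.** The protocol commits to enrolling every eligible child seen, by the same wording in both arms and regardless of FAM-CARE participation. A reader might infer that staff pick children at their discretion; no passage gives them that discretion. What stands is narrower: the commitment runs through referral by staff who know the arm, and nothing in the protocol verifies it against the register.

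**Share enrolled.** A reader might infer that most eligible children are left out. Table 2 does not support this. It counts all children on ART at the end of 2015, not eligible children at enrolment, and on the protocol's 10-20% figure a majority of eligible children are enrolled. Entry also requires a relative receiving services at the same facility, so fewer may qualify. If only 60% were eligible and 80% of those consented (both assumed), 1196 × 0.6 × 0.8 = 574 children would be available for the 666 × 0.85 = 566 needed on ART, and little room for selection would remain. The protocol does not give the actual share.

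**Attendance.** The one-collector rule has its dose-adjustment exception. Monthly paediatric visits are described as standard within FAM-CARE too, monitoring visits continue, and recruitment is planned over 12 months. Most children should therefore be seen eventually. The contrast between arms is weaker than the one-collector sentence alone suggests, though it is not zero if a quota closes early.

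**Size.** A reader might turn the ratios in step 5 into false-positive rates of about 14%, 33% and 69% at 199 per arm. The arithmetic is right, but those rates describe assumed ratios that run against the only documented mechanism. They also carry selection at entry undiminished to 18 months and ignore adjustment. Viral load testing had mainly been limited to suspected failure, so staff would often not know suppression status. Viral load is drawn at enrolment and can be used in adjustment, which reduces but does not exclude bias from unmeasured differences.

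**Conclusion.** The point holds as a design weakness that should be corrected, not as demonstrated bias. Staff who know the arm control referral, enrolment stops at a quota, entry is not tied to the register, and no planned comparison would show whether enrolled children differ from eligible children left out, by arm. Room for selection exists because about 283 on ART per arm is 46% and 49% of the children on ART in Table 2, or about 51-62% of eligible children if 10-20% are ineligible. This rests on Table 2 still describing the pool at enrolment and on the 10-20% assumption. Neither the size nor the sign of any bias can be derived from the protocol. The 3.3 to 8.9 point range shows only that moderate selection would matter against a 10-point target.

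**What to change.** In Recruitment, replace identification by clinic-staff referral with identification by the study nurse from each facility's HIV care/ART register. Use the same start date and the same rule in both arms: screen every registered child under 15 for eligibility, then approach every eligible child, either consecutively or in a pre-set list order, until the facility quota is met. Make the matching change in Study sampling procedures.

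Use the existing screening log to report aggregate counts by arm of children listed, eligible, approached, refused and enrolled. Counts alone require no individual data on non-participants, so this fits the Confidentiality section.

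Strict random ordering is not required, nor is contact through the relative who collects the drugs; these would add accrual and disclosure burdens. The change does not blind anyone, but it takes the decision about who is considered out of the hands of programme staff and makes coverage visible.

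The cost is a protocol and SOP wording change, some extra study-nurse time (registers may not show whether a relative is HIV-positive, so families would still have to be asked), and possibly slightly slower accrual. It must be in place before enrolment opens, because analysis cannot recover children who were never considered.
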